### Randomization and blinding

Eligible patients will be randomly assigned at a 1:1 ratio to receive either HGMX or placebo. We generated the random sequence using computer software. An independent randomization management center is responsible for sequentially assigning the random number and distributing trial samples to patients to ensure that the process of allocation is concealed. Clinicians, patients, data collectors, and outcome assessors will be blinded to the group assignment. The allocation will be unblinded if a severe adverse event occurs and when the final data analysis is complete.

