### Outcome measurements

#### Primary outcome

The primary outcome is the change in the total score of the Spleen Qi Deficiency Symptoms Grading and Quantifying scale (SQD scale). The SQD scale is a modified version of the classic scale for assessing the degree of SQD in the Clinical Guideline of New Drugs for Traditional Chinese Medicine [21]. The SQD scale consists of 17 items regarding symptoms of SQD: (1) stomach distension, (2) abdominal distension, (3) physical fatigue and weakness, (4) mental fatigue and taciturnity, (5) loss of appetite, (6) abnormal stools, (7) stomach pain, (8) stomach tightness, (9) abdominal pain, (10) acid reflux, (11) belching, (12) nausea and vomiting, (13) abnormal bowel sounds, (14) powerless defecation, (15) sallow complexion, (16) loss of taste and hypodipsia, and (17) facial and limb edema. Items 1–6 are the main symptoms; the other items are secondary symptoms. The items are assessed for duration (0–3 points, only available for items 1–2 and 7–9), severity (0–3 points, not available for item 13), frequency per day (0–4 points; 0–3 points for item 5), and frequency per week (0–5 points). The total score is the sum of the scores of each item (the main symptoms are scored twice) and ranges from 0 to 292. A higher score indicates a more severe symptom. Compared with the classic scale, we added four items (items 1, 7, 10, and 11), defined the main symptoms according to TCM theory, and assessed each item for duration, severity, and frequency per day and per week rather than only for severity. The details of the SQD scale are presented in Additional file 1.

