#### Safety outcomes

The safety outcomes are as follows:Adverse events (AEs), such as abnormal results (greater or less than 2 × normal reference interval) in routine blood, urine, and stool tests; liver function tests (alanine transaminase, aspartate aminotransferase, total bilirubin, direct bilirubin, and indirect bilirubin); kidney function tests (serum creatinine and urea nitrogen); coagulation function (prothrombin time, activated partial thromboplastin time, thrombin time, and fibrinogen); or electrocardiograms; as well as any other new-onset symptoms or diseases related or unrelated to the interventionSevere AEs (SAEs) are those AEs that lead to new or prolonged hospitalization, disability, admission to the intensive care unit, mortal danger, or death. SAEs will be reported to the principal investigator, the ethics committee of the hospital, and the Jiangxi Food and Drug Administration within 24 hWithdrawal due to AEs.

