## Statistical analysis

Data analysis will be performed with Stata v14.0 (StataCorp LLC, College Station, TX, USA). The main primary outcome analysis will be based on the intention-to-treat data set, where the missing values will not be imputed and the patients who took unscheduled medications will be kept in their original group. We will also perform four sets of sensitivity analyses to test the robustness of the results of the main analyses, including (1) using the per protocol data set; (2) imputing missing data using various methods dependent on the proportion and distribution of the missing data; (3) excluding patients who become aware of the grouping accidentally during the trial, which also aims to estimate the placebo effects; and (4) excluding patients who took unscheduled medications. The analysis of secondary outcomes will be based on the per protocol data set, and the analysis of safety outcomes will be based on the safety data set only, both with no imputation. Interim data analyses will be performed after weeks 8 and 52.

Descriptive analysis will be conducted to explore the means and standard deviations of the continuous variables. We will assess the treatment effects by comparing the mean between-group differences of the continuous endpoints with a normal distribution using the independent *t* test. The skewed continuous variables will be described using medians and interquartile ranges. We will use the Mann-Whitney *U* test to assess the equivalency of the skewed continuous variable distributions. Moreover, we will describe categorical variables through their frequencies and percentages. We will evaluate the between-group differences using Pearson’s chi-square test for the cases with expected counts greater than 5 in more than 20% of cells and greater than 1 in any cell or Fisher’s exact test otherwise. We will perform subgroup analyses stratified by gastric cancer stage and chemoradiotherapy regimen for the primary outcome. We set α = 0.05 as the nominal type I error rate, which will be adjusted for the multiple *t* test using the O’Brien-Fleming group sequential method [25].

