### Data collection and monitoring

All investigators involved in the trial will receive research training based on standard operating procedures. An independent data monitoring committee (DMC) at Jiangxi University of Traditional Chinese Medicine will be founded and be responsible for supervising the entire trial process. Data collection, such as questionnaire surveys, physical examinations, biological samples, and laboratory examinations, will be performed by qualified physicians at each research center. Student volunteers, as clinical research coordinators, from Jiangxi University of Traditional Chinese Medicine will be in charge of contacting patients for timely follow-up. Each research hospital will have a clinical research associate from the Jiangxi University of Traditional Chinese Medicine who will be in charge of monitoring patient compliance and case report form completeness and will address issues during the trial. The original case report forms will be inputted into the online database by two clinical research coordinators in duplicate. Personal information for all patients will be anonymized. The database will be password protected and will be managed by the DMC. An independent analyst will have access to the database only during the data analysis period. The DMC will also have the authority to discontinue the entire trial according to the following standards: (1) HGMX does not show any efficacy toward SQD symptoms up to 8 weeks of follow-up, as indicated by an absolute difference < 5 on the SQD scale score between the two groups (this difference is estimated based on the unpublished results of our other trial assessing HGMX for nonorganic gastrointestinal disorders); (2) HGMX does not show statistically significant efficacy for any outcome up to 52 weeks of follow-up compared with placebo; and (3) any severe AE related to HGMX occurs.

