## Discussion

Some previous RCTs assessed the effects of Shen Ling Bai Zhu San, the basic formula of HGMX, for treating patients with gastric cancer. These RCTs showed promising results, such as reduction in the incidence and severity of postoperative ileus, irritable bowel syndrome, and anemia [26], remission of gastrointestinal symptoms [27], and improvement in quality of life [28], which could also support the efficacy of HGMX to some degree. However, all of these RCTs had a short treatment course (≤ 8 weeks) and were at high risk of selection and performance bias due to a lack of reporting of information regarding allocation concealment, blindness, and data monitoring. Therefore, high-quality RCT evidence is warranted regarding the efficacy of HGMX for patients who have undergone radical gastrectomy for gastric cancer.

This RCT aims to clarify whether HGMX, as a dietary formula based on TCM theory, is effective and safe for improving SQD syndrome, quality of life, performance status, and prognosis of patients with gastric cancer who have undergone radical gastrectomy. To improve the quality of study reporting and conduct, we will develop a standard operating procedure manual according to the principles of the Consolidated Standards of Reporting Trials Extension for Chinese Herbal Medicine Formulas [29] and will thoroughly train all investigators. A potential limitation of this trial is that we will use a modified version of the classic SQD scale that has not been validated (no reliability or validity evaluation).

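### Every severe adverse event breaks the blind, including an admission unrelated to the product, although later symptom scores stay in the primary analysis and relatedness need not be recorded first

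*Protocol article*

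**What the plan says.** All references are to the protocol article.

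- **Randomization and blinding.** On who is blinded: "Clinicians, patients, data collectors, and outcome assessors will be blinded to the group assignment". On when the blind ends: "The allocation will be unblinded if a severe adverse event occurs and when the final data analysis is complete". The section sets no condition on relatedness or need, and does not say who is told.
- **Safety outcomes.** Severe adverse events are those that "lead to new or prolonged hospitalization, disability, admission to the intensive care unit, mortal danger, or death". The definition of an adverse event in the same section takes in new symptoms and diseases irrespective of cause.
- **Compliance and withdrawal.** The listed reasons are progression with renewed cancer therapy, recurrent surgical complications, continuing deterioration of the syndrome, poor compliance and the patient's own choice. A severe adverse event as such is not listed.
- **Statistical analysis.** "The main primary outcome analysis will be based on the intention-to-treat data set, where the missing values will not be imputed". Sensitivity analysis 3 consists of "excluding patients who become aware of the grouping accidentally during the trial, which also aims to estimate the placebo effects".
- **Data collection and monitoring.** One of three grounds on which the data monitoring committee (DMC) may discontinue the trial is that "any severe AE related to HGMX occurs".
- **Discussion.** On the primary outcome measure, the authors concede that "we will use a modified version of the classic SQD scale that has not been validated".

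**The concern.** A code-break usually serves a particular patient whose care depends on knowing the treatment. Here the trigger is the occurrence of the event, so the blind is given up in cases where knowing the arm serves no purpose.

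Two things are at stake. The first is the primary outcome. Most of the 17 items are symptoms such as fatigue, distension, appetite and tightness, where a patient or assessor who knows the arm can shift the score without intending to. The second is the attribution of harm. A single severe event judged related to the product gives the DMC authority to end the trial, and that judgement is more credible if made before the arm is known.

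**Working it through.** **1. How wide is the trigger?** The unblinding rule refers to any severe adverse event. The safety section makes an event severe if it causes an admission, and makes it an adverse event whether or not the product is involved. Together, an admission for a new, unrelated illness opens the code. This follows from two stated rules and does not depend on missing detail.

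**2. Do scores given after unblinding reach the primary analysis?** Visits run to week 104. A patient admitted for an unrelated illness meets none of the listed withdrawal reasons on that ground alone, and so continues to complete the scale. The main analysis is by intention to treat and has no rule for scores given after unblinding, so those scores can count.

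**3. Is relatedness protected?** The stopping ground turns on relatedness to HGMX. The article does not fix the order of the two steps, recording causality and opening the code.

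**4. The plan's own sample size.** Inputs from Sample size estimation: difference 8.0, SD 14.5, alpha 0.05 (taken as two-sided), power 0.80, dropout 20%.

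n per arm = 2 × [14.5 × (1.960 + 0.842) / 8]² = 51.6, rounded up to 52. Then 52 / (1 − 0.20) = 65 per arm, or 130 in total. The stated figure reproduces and is not in dispute.

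**5. Illustration of size.** The article gives no severe-event rate, so both inputs below are assumptions. Let r be the share of patients with at least one severe event in 2 years, taken as equal in the two arms. Let b be the shift that unblinding causes in the between-arm difference among those patients. The overall shift is r × b.

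| r (assumed) | Patients of 130 | Shift if b = 4 | Shift if b = 8 |
|---|---|---|---|
| 5% | 6.5 | 0.2 | 0.4 |
| 10% | 13 | 0.4 | 0.8 |
| 20% | 26 | 0.8 | 1.6 |
| 30% | 39 | 1.2 | 2.4 |

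Against the planned difference of 8, the range is 0.2/8 = 2.5% to 2.4/8 = 30%. The table assumes that every unblinded patient gives a score after the event at the analysed visit. If a share w of them leaves first, their weight falls from r to r(1 − w)/(1 − rw), which is always smaller. Scores recorded before the event are unaffected.

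**6. Sensitivity analysis 3.** The trial compares HGMX with placebo and has no untreated arm. Removing patients who learned their group leaves an HGMX–placebo contrast in a subgroup formed after randomization. A placebo effect is a contrast between placebo and no treatment, which this design does not contain. Any change from the main result would mix expectation with selection. This holds whoever is in the excluded group.

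**The case against.** The strongest reply is that a journal article condenses a longer protocol. Who is told, when causality is judged and how code-breaks are logged are details that protocol version 3.2 or the operating manual may settle. That stands for those details: their absence from the article does not show that attribution is made, or scores are given, with the arm known. It does not answer the rule itself, which is stated without condition.

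Three further points carry weight.

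- **Frequency.** A reader might infer that many patients will be unblinded. The article gives no rate, and it excludes stage IV disease, ECOG above 1 and other severe illness. Some patients admitted for relapse will be withdrawn for progression with renewed therapy, and their missing scores are not imputed in the main analysis. The upper rows of the table are therefore not forecasts.
- **Sensitivity analysis 3.** A reader might infer that it removes patients unblinded after a severe event. It covers only those who learn their group accidentally, and unblinding under the rule is planned. On the plain wording they are not excluded.
- **Stopping.** The DMC has authority to stop and is not obliged to. An event in a placebo patient cannot be related to HGMX, so the arm must be known at some level to apply the ground. Both are true. The investigator can still record whether the event is related to the study product while blinded, with the arm added by the DMC afterwards.

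**Conclusion.** The point holds as a weakness in a stated rule. Following the article as written breaks the blind for unrelated admissions, leaves those patients contributing to a subjective primary outcome, and does not protect the relatedness judgement on which a stopping ground depends. Bias in the score and in attribution is a risk and not an established fact, because the article does not say who is told or when relatedness is judged.

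The range in the table rests wholly on assumed rates and shifts. It shows that the effect could be anything from negligible to material, and does not estimate it. The sample size is unaffected. The placebo-effect claim in sensitivity analysis 3 is a separate and smaller error that does not depend on the unblinding rule. The change should be made, because the trial's double-blind claim rests in part on this sentence.

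**What to change.** Replace the unblinding sentence with a rule to this effect:

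- the code is opened for a single patient only when the allocation must be known for that patient's care or for regulatory reporting;
- the investigator records relatedness before it is opened;
- outcome assessors, and where possible the patient, remain blinded;
- every opening is logged;
- the DMC may review severe events by arm.

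If the full protocol already contains any of these safeguards, the sentence should be brought into line with it.

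In Statistical analysis, delete the placebo-effect aim from sensitivity analysis 3, and state that patients unblinded under the severe-event rule do not count as accidentally aware and are not excluded there. A question asking all patients to guess their treatment would be a useful optional addition: the article concedes a slight difference in taste and smell, although its simulation test suggests that the products cannot be told apart.

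The cost is a wording amendment and, if wanted, one questionnaire item. Emergency unblinding remains available, and neither the sample size nor the main analysis changes.

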### Interventions and concomitant treatments

Eligible patients will receive either 30 g/day HGMX or 30 g/day placebo taken orally for 2 years. Every 30 g of HGMX contains 10.1 g of herbal materials. The placebo consists of early rice and oats and is identical to HGMX in terms of preparation, packaging, labeling, and color but is slightly different in taste and smell; according to our simulation test, the two treatments should be impossible to distinguish. The test samples will be distributed to patients once per month. Other Chinese herbal medicines and Western drugs to treat gastrointestinal symptoms (e.g., proton pump inhibitors, prokinetics) are prohibited. The patients will be asked to sign an integrity commitment; they should truthfully report whether they used a treatment outside the regimen at any time. This information will be recorded and used for sensitivity analyses.

Both groups will undergo surveillance of gastric cancer according to the Japanese Gastric Cancer Treatment Guidelines 2014 [4] and continuous concomitant care for other comorbidities (such as hypertension, diabetes mellitus, and osteoarthritis) during the study follow-up period. Concomitant treatments will be recorded at each visit.

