## Background

Although the incidence of gastric cancer is decreasing annually because of the popularization of *Helicobacter pylori* detection and eradication and improvements in living conditions, it represents one of the largest disease burdens worldwide [1]. According to the statistics reported by the World Health Organization in 2016, gastric cancer accounts for 1.53% of deaths worldwide, second only to lung cancer [2]. Due to the high *H. pylori* infection rate, dietary habits, and susceptibility genes, approximately 50% of gastric cancer cases worldwide occur in East Asian populations [3].

Radical gastrectomy, the standard treatment with a curative intent for patients with early-stage gastric cancer, can substantially prolong disease-free and overall survival [4]. However, chronic complications after the surgery and adjuvant chemoradiotherapy, such as chronic gastrointestinal disorders (e.g., abdominal distension and diarrhea) and general symptoms (e.g., physical fatigue and mental issue), are common and may lead to discomfort, malnutrition, hypoimmunity, decreased quality of life, and even cancer relapse [5]. Although the management of chronic complications is crucial for improving the prognosis of patients with gastric cancer, there are no specific interventions in the current guidelines for treating the complications except for surveillance and nutritional support [4, 6, 7]. Therefore, alternative and complementary therapies are popular in clinical practice [8, 9]; in particular, traditional Chinese medicine (TCM) is widely used to treat postgastrectomy complications in China, which has the heaviest disease burden of gastric cancer globally [10–12].

In TCM theory, the spleen (also written as “pi”, an abstract digestive organ in TCM that differs from the Western medical definition of the spleen as an immune organ) is responsible for transporting food and water, and qi is the vital life force produced by vital activity [13]. Patients who have undergone radical gastrectomy and chemoradiotherapy can easily suffer damage to the spleen and qi, leading to a spleen qi deficiency (SQD) syndrome, the typical symptoms of which include stomach and abdominal distension, dyspepsia, chest and stomach distress, borborygmus, diarrhea, fatigue, weakness, and weight loss [11, 14].

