### Other assessments

Demographic profiles and histories of patients will be recorded at the baseline visit, including sex, age, marital status, education level, smoking and drinking habits, comorbidities, pathological type of gastric cancer, gastric cancer stage, type of resection surgery, chemoradiotherapy regimen, and medication history for the past 3 months.

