### Study visits and outcome assessments

The duration of follow-up will be 2 years. Patients will visit at baseline and at 2, 4, 8, 26, 52, 78, and 104 weeks. At each visit, questionnaires and physical examinations will be completed, self-reported AEs will be recorded, and compliance will be assessed. At 8, 26, 52, 78, and 104 weeks, laboratory examinations and electrocardiograms will be performed, and cancer progression will be assessed. A detailed schedule of the trial is presented in Fig. 2.

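### The ban on gastrointestinal drugs and other herbal medicines is not tied to the baseline SQD score, so patients who stop such a drug at entry add noise, though not expected bias, to the primary change score

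*Protocol article*

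**What the plan says.** Under Interventions and concomitant treatments, the protocol article states: "Other Chinese herbal medicines and Western drugs to treat gastrointestinal symptoms (e.g., proton pump inhibitors, prokinetics) are prohibited". It does not say when the ban begins relative to the baseline assessment.

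Patient eligibility lists detailed inclusion and exclusion criteria. None mentions current or recent use of these products. The only minimum interval, 2 weeks, concerns surgery, radiotherapy, chemotherapy and treatment of surgical complications.

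The schedule runs directly from baseline to week 2: "Patients will visit at baseline and at 2, 4, 8, 26, 52, 78, and 104 weeks".

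The primary outcome is the change in total SQD score. Its items include distension, abnormal stools, acid reflux, belching and nausea.

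Under Other assessments, the baseline record includes "medication history for the past 3 months", but the article states no use for it in eligibility, stratification or analysis.

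Statistical analysis plans to assess treatment effects by "comparing the mean between-group differences of the continuous endpoints with a normal distribution using the independent *t* test", with no covariate named. The sensitivity analysis on medication is "4) excluding patients who took unscheduled medications".

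**The concern.** The banned products are taken for symptoms that the SQD scale scores. If a patient is using one when baseline is scored and then complies with the ban, the baseline is lower than it would be untreated, and the later change mixes the effect of the test sample with the loss of the earlier drug. Treated symptoms may also go uncounted when SQD is diagnosed at entry.

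Prior use is foreseeable. The Background says "traditional Chinese medicine (TCM) is widely used to treat postgastrectomy complications in China", and the baseline record asks about recent medication. The planned analyses do not pick the problem up. The t test has no covariate, and the medication sensitivity analysis is about unscheduled use, not about a drug stopped at entry.

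At stake are the interpretation of change within each arm, the precision of the primary comparison, and the early visits. A withdrawal effect is most plausible at weeks 2 to 8, and week 8 is when the data monitoring committee may stop the trial if the groups differ by less than 5 points.

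**Working it through.** **Inputs from the article** (Sample size estimation; Data collection and monitoring): difference 8.0, SD 14.5, α 0.05, power 0.80, dropout 20%, total 130 (65 per group); week-8 threshold 5 points. Sidedness is not stated. Two-sided reproduces the total; one-sided would need only 41 per arm before dropout.

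**Inputs assumed, not in the article:** p, the share of entrants who stop a banned product at baseline, 0.1 to 0.4; d, the resulting rise in their SQD score, 5 to 15 points.

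**Step 1. Reproduce the plan's figure.** n per arm = 2 × (1.960 + 0.842)² × 14.5² / 8² = 51.6, so 52. With dropout, 52 / 0.80 = 65 per arm, 130 in total. Power at 52 per arm = Φ(8 / (14.5 × √(2/52)) − 1.96) = Φ(2.813 − 1.96) = 80.3%. The stated size is reproduced.

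**Step 2. Expected between-arm difference.** With 1:1 randomisation and the same withdrawal effect in both arms, each arm's mean change moves by p × d, and this cancels in the difference. A simulation of 20,000 trials at p = 0.3, d = 10 and a true difference of −8 gave a mean difference of −7.98.

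**Step 3. Variance, power and chance imbalance.** If a share p of patients is shifted by d, then

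- SD′ = √(14.5² + p(1−p)d²)
- power = Φ(8 / (SD′ × √(2/52)) − 1.96)
- SD of the chance imbalance between arms = d × √(2p(1−p)/52)

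| p | d | Shift in both arms (p × d) | SD′ | Power | SD of chance imbalance |
|---|---|---|---|---|---|
| 0.1 | 5 | 0.5 | 14.6 | 79.9% | 0.3 |
| 0.2 | 10 | 2.0 | 15.0 | 77.4% | 0.8 |
| 0.3 | 10 | 3.0 | 15.2 | 76.5% | 0.9 |
| 0.4 | 15 | 6.0 | 16.3 | 70.9% | 1.4 |

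Last row in full: 210.25 + 0.24 × 225 = 264.25, whose root is 16.26; 8 / (16.26 × 0.1961) = 2.51; Φ(2.51 − 1.96) = 70.9%. Imbalance: 15 × √(0.48/52) = 1.44.

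**Step 4. Week-8 rule.** With a true difference of 8 and 52 per arm (assumed also to apply at week 8), the chance of observing a difference below 5 is Φ(−3 / (SD × √(2/52))). This is 14.6% at SD 14.5 and 17.3% at SD 16.3.

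**Step 5. What adjustment would recover.** If a flag identified exactly the shifted patients, the term p(1−p)d² would leave the residual variance. The SD would return to 14.5 and power to about 80%. An imperfect flag recovers part of this.

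**The case against.** The strongest reply is that this is a silence in a condensed article. The full protocol (version 3.2) and the schedule figure are not shown, and either may say what happens before baseline. That limits the point to what the article fixes. But the article prints eligibility in fine detail, including an interval for other treatments, and pairs it with a ban and a change score without saying how they connect. The request for clarification stands.

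Several further objections are correct and limit the point:

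- A reader might infer a biased treatment effect. Allocation is randomised and blinded, so the shift cancels in expectation unless the test product acts differently in patients coming off a drug. The article gives no ground for assuming that.
- A reader might infer that prior use of all these drugs is common. The Background sentence on wide use is about traditional Chinese medicine, not proton pump inhibitors or prokinetics. The Discussion expects additional medicine to be needed infrequently in patients with ECOG ≤ 1. It gives no figure and speaks of need during the trial, but it favours the low end of the range.
- A reader might infer that every such patient is off the drug throughout follow-up. This holds only for those who comply; those who continue stay in the intention-to-treat set.
- The SD of 14.5 comes from a preliminary study and expert advice. If those patients had similar prior use, part of the extra variance is already in it.
- The upper assumption for d, 15 points, is larger than the 8-point effect the trial is built on. The upper end is a stress case, not an estimate.
- That the medication history is never used cannot be shown. The article states no use, but a statistical analysis plan may.

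**Conclusion.** The point holds in a limited form. The ban, the eligibility criteria, the schedule without a run-in and the change-score outcome together let a patient be scored on treatment at baseline and off it afterwards, and the stated analysis does not account for this. The expected between-arm difference stays at 8. The cost is in within-arm change, precision and chance imbalance.

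The size depends on two assumed quantities. At p = 0.1 and d = 5, almost nothing is lost (power 79.9% against 80.3%). At p = 0.4 and d = 15, power falls to about 71%, and a one-SD chance imbalance moves the estimate by 1.4 of the assumed 8 points. The rise in the chance of missing the week-8 threshold, from 14.6% to at most 17.3%, is modest. That the effect is greatest at weeks 2 to 8 is a plausible inference, not a documented fact.

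This merits a clarification and an inexpensive change to the analysis. It does not show that the trial's comparison is invalid.

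**What to change.** 1. Reconcile Patient eligibility with Interventions and concomitant treatments by stating whether the ban applies before SQD diagnosis and baseline scoring. Any interval, and what happens to a patient using such a product, is for the sponsor to set. Trial status reports 80 of the planned 130 already enrolled at submission, so a new entry rule would give early and late entrants different baseline conditions; that should be weighed.
2. For all patients, derive a flag for use of a banned product at baseline from the 3-month medication history. Include it as a covariate in the primary comparison, for example in a linear model with treatment and the flag, in place of the unadjusted t test. Define it before unblinding. The history must show whether a product was still in use at baseline; if it shows only use within the 3 months, the flag is cruder and recovers less.
3. Add a sensitivity analysis excluding flagged patients. The flag describes use before randomisation, so this keeps a randomised comparison among those who remain.

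The cost is one clarifying sentence, one derived variable and slightly more analysis work. The sample size stays at 130. The gain is small if prior use is rare.
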